## Abstract

**Background:**

Progression of dental caries can result in irreversible pulpal damage. Partial irreversible pulpitis is the initial stage of this damage, confined to the coronal pulp whilst the radicular pulp shows little or no sign of infection. Preserving the pulp with sustained vitality and developing minimally invasive biologically based therapies are key themes within contemporary clinical practice. However, *root canal treatment* involving complete removal of the pulp is often the only option (other than extraction) given to patients with irreversible pulpitis, with substantial NHS and patient incurred costs. The European Society of Endodontology’s (ESE 2019) recent consensus statement recommends *full pulpotomy*, where the inflamed coronal pulp is removed with the goal of keeping the radicular pulp vital, as a more minimally invasive technique, potentially avoiding complex root canal treatment. Although this technique may be provided in secondary care, it has not been routinely implemented or evaluated in UK General Dental Practice.

**Method:**

This feasibility study aims to identify and assess in a primary care setting the training needs of general dental practitioners and clinical fidelity of the full pulpotomy intervention, estimate likely eligible patient pool and develop recruitment materials ahead of the main randomised controlled trial comparing the clinical and cost-effectiveness of full pulpotomy compared to root canal treatment in pre/molar teeth of adults 16 years and older showing signs indicative of irreversible pulpitis. The feasibility study will recruit and train 10 primary care dentists in the full pulpotomy technique. Dentists will recruit and provide full pulpotomy to 40 participants (four per practice) with indications of partial irreversible pulpitis.

**Discussion:**

The Pulpotomy for the Management of Irreversible Pulpitis in Mature Teeth (PIP) study will address the lack of high-quality evidence in the treatment of irreversible pulpitis, to aid dental practitioners, patients and policymakers in their decision-making. The PIP feasibility study will inform the main study on the practicality of providing both training and provision of the full pulpotomy technique in general dental practice.

**Trial registration:**

ISRCTN Registry, ISRCTN17973604. Registered on 28 January 2021.

Protocol version

Protocol version: 1; date: 03.02.2021

**Supplementary Information:**

The online version contains supplementary material available at 10.1186/s40814-022-01029-9.

## Background

The economic burden of dental disease to the NHS, patients and society is substantial, accounting for a global expenditure of $544.41bn annually [1]. NHS expenditure on dental care in England exceeds £3bn per year and £527 million in Scotland [2]. Most of this expenditure is due to dental caries, one of the most prevalent non-communicable diseases worldwide [3–6]. The consequences are cumulative [7, 8] and can negatively impact the quality of life and productivity.

Most adults experience decay, and the National Dental Epidemiology Programme for England 2018 reported that 90% of adults have at least one restoration [9]. Dental caries results in localised and progressive demineralisation of the dental hard tissue; if undisturbed, the bacterial insult will cause the pulp of the tooth to become inflamed and persistent inflammation can lead to *irreversible pulpitis* (when the vital inflamed pulp is incapable of healing) [10], *pulp necrosis* and *abscess* formation. Management of dental caries centres around primary prevention and/or operative intervention involving caries removal prior to the irreversible pulpitis stage. Preserving the pulp in a healthy state with sustained vitality, preventing apical periodontitis or abscess formation and developing minimally invasive biologically based therapies are key themes within contemporary clinical practice.

The recent position statement from the European Society of Endodontology (ESE 2019) [11] explains the challenge of managing deep caries and pulp exposure. If primary prevention and/or operative intervention involving caries removal prior to irreversible pulpitis fails, *root canal treatment* (*RCTx*) involving complete removal of the pulp is the only option (other than extraction) for patients with irreversible pulpitis, but it is a technically demanding procedure, especially in premolar and molar teeth and increases patient anxiety [12]. It is also time-consuming and costly to the NHS and patients. In Scotland, 111,000 RCTxs were provided in 2017/2018, costing £8.9m, and approximately 80% of this cost relates to RCTxs on premolar and molar teeth. Extrapolating these figures to England suggests the total cost of this treatment may be in excess of £71m per year.

Partial irreversible pulpitis is the initial stage of irreversible pulp damage, confined to the coronal (crown) pulp whilst the radicular (root) pulp remains vital, i.e. a healthy blood supply is maintained to the pulp tissue in the roots of the tooth. The full pulpotomy (FP) technique of removing the coronal pulp may keep the radicular pulp vital. Systematic reviews and randomised controlled trials suggest that pulpotomy may offer comparable treatment success rates and might be a cost-effective alternative to RCTx, but the evidence base is weak and sparse for the management of vital mature teeth with clinical signs of irreversible pulpitis in the UK NHS [13–16]. Two randomised controlled trials conducted in an adult population reported a success rate of pulpotomy comparable to RCTx (97.6% vs 98.3% at 1 year [17]; 85% vs 87.5% at 18 months [18]). However, both trials were conducted outside of the UK and in the secondary care setting. These studies have limited generalisability due to the lack of methodological rigour, difference in the health systems and the clinical approaches used. There is one ongoing trial in the UK [19] looking at this research question in a secondary care setting.

RCTx success rates vary considerably in the literature. A systematic review [20] together with recent studies conducted internationally [21–23], including primary and secondary care, concluded that the 2- to 10-year survival outcomes of RCTx ranged from 72 to 94.4%. Treatment success rates in primary care dentistry in Sweden, according to periapical status, was 62% immediately after treatment [24]; however, a review on RCTx survival in general dental services in England and Wales estimated 74% of root canal treated teeth pass through 10 years without re-treatment, apical surgery or extraction, and the success rate is above 90% in the first year [22]. Evidence from a systematic review and a retrospective follow-up study suggests that the success rate of pulpotomy for permanent posterior teeth may be over 90% at 1-year follow-up, but the participants in the included studies were not representative of UK NHS practice [13, 25].

The recently published commissioning standard in NHS England Restorative Dentistry defined the complexity of clinical and technical procedures according to levels of care 1, 2 and 3 (with increasing complexity). They also reflected the competency of clinicians and the equipment required to deliver care of that level of complexity [26]. Complex RCTxs are considered levels 2 and 3 and should be referred to specialists or dentists with special interest. FP could make the management of complex cases possible in primary care by general dental practitioners (GDPs), avoiding the need for extraction or the increased cost and burden on patients in referral.

FP is a novel technology for NHS primary dental care, and the Pulpotomy for the Management of Irreversible Pulpitis in Mature Teeth (PIP) feasibility study design has benefited from considerable active and informative input from patients in general dental practice, the Health Services Research Unit (HSRU) public involvement group and a national survey of GDPs and practitioners with research experience.

The importance of this topic to GDPs in the UK is clear from the responses to a survey hosted on the Scottish Dental Practice Based Research Network (SDPBRN) website, indicating that GDPs were very interested in the health technology to be tested in PIP but that clinical training would be required for both FP and RCTx. The survey showed that pulpotomy was not offered to NHS adult patients by 91% of the responding dentists with many citing contract restrictions and the costs of bio-ceramic materials as barriers. Overcoming these issues for PIP had already been discussed with UK Chief Dental Officers. Whilst the majority of dentists (97%) offered RCTx for uncomplicated teeth, this reduced to 68% and 20% for teeth with a moderate or complex risk of adverse outcomes, respectively. In addition, the PIP study team engaged with patient representatives and the public who highlighted the need to develop more modern dental techniques which aim to preserve rather than remove tooth tissue.

The COVID-19 pandemic has had a significant impact on the provision of dental care.

RCTx is commonly completed over several visits, whereas FP treatment is usually completed in one. FP may therefore reduce patient contact within a dental practice, as well as reducing the volume and cost of personal protective equipment required.

The PIP feasibility study has been designed to determine progression to a pragmatic, primary dental care, multi-centre, two-arm patient randomised control trial with an internal pilot comparing the clinical and cost-effectiveness of FP compared to RCTx in pre/molar teeth of adults 16 years and older showing signs indicative of irreversible pulpitis.

The following are the feasibility study objectives:To identify training needs of GDPs to undertake FPTo develop a clinical training package for study GDPsTo assess if the intervention can be optimally delivered in routine NHS practiceTo estimate the number of eligible patients per practice for the main trialTo develop recruitment materials for the main trial accounting for patient and dentist views

## 
Methods/design

The PIP feasibility study is a multi-centre non-randomised intervention designed to determine if it is feasible to carry out FP in the UK NHS primary care setting.

### Study recruitment and allocation

#### Recruitment of dentists

We aim to recruit 10 GDPs with research experience from across the UK via our partner research networks and dentists who may or may not be active in other dental trials. Working with research-ready and experienced dentists will help us speedily identify training needs, service requirements and criteria for successful intervention delivery. A list of participating practices will be kept up to date and provided on the public trial website: https://w3.abdn.ac.uk/hsru/pip.

Following the expression of interest, an appraisal of each practice’s ability to recruit participants will be conducted including evidence of a sufficient supply of eligible patients from their routine patient base or new patient population. Digital X-ray facilities at the practice will be preferred but are not essential.

#### Identifying and recruiting participants

GDPs will identify patients presenting at their clinic/practice with symptoms indicative of irreversible pulpitis who meet the inclusion criteria. Patients with these symptoms who contact the practice by telephone will be informed the trial is taking place by the practice receptionist. An appointment will be arranged for potentially eligible patients (as per current clinical practice) for their treatment, and those who express interest in the feasibility study will be given a participant information leaflet (PIL) (Additional file 1). In the event that a patient presents at an appointment requiring immediate treatment, sufficient time to make an informed decision regarding willingness to participate will be given. At the treatment visit, the patient will be given the opportunity to clarify any questions prior to informed consent being provided on the study consent form (Additional file 2).

#### Allocation

Treatment options for irreversible pulpitis will be discussed with the patient and each recruited participant will be offered the FP treatment in the first instance. Should the dentist feel another treatment is more appropriate or a recruited participant changes their mind and does not want a FP, the appropriate alternative treatment should be carried out as per normal practice.

After the initial intervention, participants will receive any treatment deemed clinically appropriate by their dentist as per normal practice.

#### Inclusion criteria

One of the inclusion criteria is adults (16 years and older) with symptoms indicative of irreversible pulpitis in a pre/molar tooth with deep caries and/or a deep restoration as defined by ESE as spontaneous, radiating pain that lingers after removal of stimulus [11].

#### Exclusion criteria

The following are the exclusion criteria:Tooth with immature roots, clinical or radiographic signs of a necrotic pulp or a poor prognosis (e.g. internal or external resorption)Presence of a sinus, tenderness to percussion, buccal tenderness, pathological mobility or evidence of pathology on a periapical radiographInsufficient tooth tissue for a restorationAll treatment delivered under a private contractUnable to give informed consent

### Intervention

The following are the full pulpotomy procedure:Pre-operative peri-apical radiograph.Access cavity preparation.Where caries removal is necessary, this should be complete and carried out in a systematic way removing it completely at the periphery of the cavity then progressively over the pulp, for a controlled reduction in the bacterial load preventing further bacterial contamination of the pulp.Rubber dam should be applied prior to accessing the pulp chamber.Once the pulp has been reached, a new sterile bur or sharp sterile excavator should be used with a water coolant to remove the pulp to the level of the radicular/root canal orifices.The dentist should confirm that all root canals are vital.Haemostasis and disinfection should be achieved by placing cotton pellets soaked with 5% sodium hypochlorite over the pulp stump for up to 5 min.If haemostasis cannot be achieved after 5 min, the tooth should undergo pulpectomy and RCTx as per the clinician’s normal practice.Once haemostasis has been achieved for all root canals, a hydraulic calcium silicate cement should be placed directly onto the pulp tissue.The tooth is definitively sealed immediately to prevent micro-leakage. Immediate post-operative radiograph is taken for FP after the placement of definitive restoration. This radiograph will be used to confirm fidelity to the FP procedure to confirm that there is adequate coverage and thickness of hydraulic calcium silicate cement in the floor of the pulp chamber and pulp stumps and absence of porosity and the tooth is definitively sealed.

Clinical fidelity to the protocol will be assessed by the study’s clinical team. The clinical team will use the criteria below to evaluate the post-operative radiographs uploaded to the trial website by the participating dentists. Ultimately, the decision as to whether fidelity with the protocol has been maintained is a clinical judgement, made by the clinical team.

The following are the clinical fidelity criteria:Access cavity preparation (complete removal of the pulp chamber roof).Adaption of the calcium silicate cement (Biodentine). The cement should cover the floor or pulp stumps and have an adequate thickness of 2mm, and no porosities should be present.Adequate final restoration (no excess Biodentine on the walls preventing peripheral seal).

### Training in the delivery of intervention

Training will be provided over two sessions. One session will be a remote training session in which all dentists recruited to the feasibility study will receive training in the background and evidence for FP, diagnosis of irreversible pulpitis and study inclusion and exclusion criteria, along with theoretical training in the FP technique. The next session will be a face-to-face training session at each clinical centre. Study dentists will attend the face-to-face training session at their nearest clinical centre. We will confirm and identify the training needs of GDPs to inform the development of the training package for the full trial. PPI members will be invited to the remote training event to contribute to discussions of training and recruitment.

As FP will be a new technology to most participants, instruction will demonstrate the procedure and establish the standard level of care. Instruction in access cavity preparation and choice of materials will include a hydraulic calcium silicate cement (e.g. Biodentine). Artificial 3D printed teeth (Fig. 1) are routinely used for RCTx training, but their use in the training in the FP technique and assessment of the success of training in the procedure is novel. We estimate 4 teeth for each dentist will be sufficient for them to feel confident and competent in the technique.

**Fig. 1 Fig1:**
[figure not shown]
Example of the sectioned Endo Reality 3D tooth showing FP

The participating GDPs’ success in training will be determined using the FP training criteria below to evaluate both the FP procedure carried out on the 3D teeth and the post-operative radiographs taken of the 3D teeth. Formative assessment for the dentists will include self-assessment using a success checklist measuring success against the same criteria. Ultimately, the decision as to whether a dentist has been successfully trained in the FP technique is a clinical judgement made by the study’s clinical team.

The following are the FP training criteria:Access cavity preparation (complete removal of the pulp chamber roof)Adaption of the calcium silicate cement (Biodentine) (covers the floor or pulp stumps, adequate thickness of 2mm, no porosity)Adequate final restoration (no excess calcium silicate cement (Biodentine) on the walls preventing peripheral seal)

### Primary outcome measures

Feasibility outcomes are set out in Table 1. These criteria will be assessed in the feasibility study in order to determine the progression to the main trial and a randomised controlled trial comparing the clinical-effectiveness and cost-benefit of FP compared to RCTx in pre/molar teeth of adults 16 years and older showing signs indicative of irreversible pulpitis.

**Table 1 Tab1:**

Feasibility criteria

Green—automatic progression. Amber—identify remediable factors and submit a recovery plan to the funder with new targets for the following 6 months. Red—stop the trial unless there is a strong case that unanticipated remediable factors have been identified and can be addressed

### Data collection and processing

An anonymised screening log has been created for the purposes of the PIP feasibility study data collection assessing the number of potentially eligible patients seen per month by each GDP.

Screening log data will either be entered into the database by the designated team members working in each site or sent to the Trial Office for entry into the database depending on practice circumstances. The staff in the Trial Office will work closely with the dental team members to ensure that the data are as complete and accurate as possible. Extensive range and consistency checks by the Trial Office will further enhance the quality of the data.

Participants who lose the capacity to consent during the study will be withdrawn. Identifiable data already collected with consent would be retained and used in the study. No further data will be collected or any other research procedures carried out on or in relation to the participant.

### Baseline characteristics

Age and gender will be recorded on the participant details form. Pre-operative periapical radiographs (if clinically needed) will be collected as part of routine care, but copies will be provided to the study team to confirm the exclusion of signs of pulpal and apical pathology.

### Trial process outcomes

The number of GDPs recruited will be assessed as the total number of GDPs that accept to take part in the study.

Success on training in FP with 3D teeth will be assessed according to the following criteria:Access cavity preparation (complete removal of the pulp chamber roof)Adaption of the calcium silicate cement (Biodentine) (covers the floor or pulp stumps, adequate thickness of 2mm, no porosity)Adequate final restoration (no excess calcium silicate cement (Biodentine) on the walls preventing peripheral seal)

The number of potentially eligible patients seen per month per GDP will be assessed as the total number of eligible patients recorded in the screening log by the GDP divided by the total number of GDPs taking part in the study.

### Clinical outcomes

Clinical fidelity with FP intervention in the feasibility study will be assessed by the study’s clinical team. The clinical team will use the criteria below to evaluate pre-operative and post-operative radiographs uploaded to the trial website by the participating dentists. Digital radiographs will be forwarded via the secure trial management system and digital images of wet films made. Ultimately, the decision as to whether fidelity with the protocol has been maintained is a clinical judgement, made by the clinical team. Each patient, from a given dentist, will be classified as complying with the clinical fidelity criteria or not. We will then calculate the percentage of patients, for each dentist, that comply with clinical fidelity. All dentists must reach the same clinical criteria set out in training to assess the feasibility of clinical fidelity with FP.

### Participant reported outcomes

Clinical success—participants satisfied with care—will be determined by patient-reported satisfaction with treatment using a question adapted from the patient-reported experience measures (PREMs) outlined in the NHS England Guide of Commissioning Dental Specialties [27]. The question is based on a scale ranging from not satisfied to completely satisfied. The intervention will be considered successful if the patient is somewhat to completely satisfied with their treatment. Participants will be contacted by their preferred method (phone, text or email) by the study office from day 7 to answer 2 questions on their satisfaction with care, experience and symptoms. Question 1: How satisfied are you with the treatment you received? Question 2: Did you have any problems in the hours after the treatment?

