### Scheduling of events

The scheduling of events is presented in Table 2.

**Table 2 Tab2:** Scheduling of events

	General dental practice approvals and training	Clinical intervention training	Screening	Baseline (initial treatment visit)	7-day follow-up	Qualitative interviews	Others
Number of general dental practitioners recruited	■	■					
Success on training in full pulpotomy		✓					
Assessment for eligibility			¥	o			
Informed consent				□			
Socio-demographic characteristics and eligibility for free treatment				o			
Clinical fidelity of the full pulpotomy intervention				o			●
Clinical success—participants satisfied with care					∞	⊕	
Dental pain and need for dental pain relief					∞		
Number of potentially eligible patients seen per month per GDP			∇				

“■” indicates general dental practitioner (GDP) signed off as greenlighted—completion of the Site Initiation Questionnaire, study approvals and training (Good Clinical Practice and clinical training)

“✓” indicates assessment by the study clinical team

“¥” indicates GDP completing the eligibility form

“o” indicates GDP completing case report form (CRF)

“□” indicates patient completing the consent form and countersigned by GDP

“●” indicates clinical post-operative radiographs

“∞” indicates phone call from the study team

“⊕” indicates qualitative interviews

“∇” indicates screening log

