### Safety concerns

Within the PIP feasibility study, only adverse events (AEs) and serious adverse events (SAEs), as determined by the site PI, that have a reasonable causal relationship to the FP treatment in the study tooth will be recorded. These will be reported to the TM who will report/escalate as necessary.

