**Fig. 2 Fig2:**
[figure not shown]
Gantt chart outlining the project timeline and milestones

Dental practice recruitment began on 9 October 2020. Follow-up assessments will take place 7 days after delivery of the FP.

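### Table 2 schedules dental pain and need for pain relief at the 7-day contact, but the printed follow-up questions name neither, and the only likely source is limited to the hours after treatment

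*Protocol article*

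**What the plan says.** Table 2 (Scheduling of events) marks two rows for the 7-day follow-up. One is satisfaction with care, which is also marked for the qualitative interviews. The other is "Dental pain and need for dental pain relief", marked in the 7-day column only. The symbol for both "indicates phone call from the study team".

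Participant reported outcomes describes the same contact. The study office makes it no earlier than day 7, using whichever of phone, text or email the participant prefers. Its purpose is for participants "to answer 2 questions on their satisfaction with care, experience and symptoms". The section then prints the two questions, "Question 1: How satisfied are you with the treatment you received" and "Question 2: Did you have any problems in the hours after the treatment". No response options or coding are given for the second.

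Milestones for the PIP Trial gives the timing again: "Follow-up assessments will take place 7 days after delivery of the FP".

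**The concern.** A schedule row promises a measurement, and the questions put to the participant have to be able to deliver it. Here the row names two things, pain and the need for pain relief, and the printed questions name neither. The question that would have to supply both looks back only to the first hours, although it is asked a week or more later.

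Lingering pain is part of the entry criterion (Inclusion criteria), and the Adverse events section lists failure accompanied by pain, infection or swelling among the events that may be expected. A participant who is comfortable on the day of treatment, then has pain from day 2 until the contact and takes painkillers throughout, could truthfully answer no to Question 2. The study would then record nothing in the one scheduled symptom row. Clinical success is defined by satisfaction alone, so that row is the only scheduled patient-reported measure of symptoms, in a study meant to inform a main trial.

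**Working it through.** No formula applies, and the plan gives no figure to reproduce. The check maps each row scheduled for the 7-day contact to the printed questions, then looks for another source.

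**Step 1: match rows to questions.**

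| Table 2 row at 7 days | Printed question | Match |
|---|---|---|
| Satisfaction with care | Question 1, satisfaction with the treatment | Direct |
| Dental pain and pain relief | Question 2, any problems in the hours afterwards | By elimination; the lead-in mentions symptoms |

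Two rows and two questions pair off, so Question 2 is evidently the intended source for the pain row.

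**Step 2: what Question 2 covers as worded.**

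- Pain in the first hours: covered indirectly, if the participant counts it as a problem.
- Pain that starts or persists after the first hours, up to the contact: outside the stem.
- Need for pain relief: not asked for any period.

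**Step 3: other sources in the article.**

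- Process data: the treatment given, its duration, visits, equipment and charges. Neither pain nor pain relief is mentioned.
- Qualitative interviews: optional for patients, qualitative, and focused on recruitment, experience and acceptability. They do not provide a measure for every participant.
- Safety concerns: only events "that have a reasonable causal relationship to the FP treatment in the study tooth will be recorded", as judged by the site. This can capture some later pain, but it is filtered by a causal judgement and is not asked of everyone. It does not measure use of pain relief.

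None of these would systematically supply the row for the 40 planned participants.

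**Step 4: mode of contact.** Table 2 gives a phone call only, while Participant reported outcomes allows phone, text or email. This matters because a caller can clarify what counts as a problem and a text message cannot. A vague stem may therefore be understood differently by mode.

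**The case against.** The strongest reply has four parts.

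- **Intended source.** The two questions are introduced as covering symptoms as well as satisfaction, and being asked about any problems after dental treatment will naturally prompt mention of pain. This stands. A reader might infer that the row has no data source at all and cannot be derived. The documents do not support that, because early pain can be reported under Question 2.
- **Unseen questionnaire.** The article condenses a fuller protocol, and response options or prompts under Question 2 may exist. This stands in part: options naming pain or painkillers would be ordinary detail to leave out, and their absence is no finding. But the article prints the stem, and options beneath it would not extend a question limited to the first hours.
- **Recall window.** The 7-day column and the day-7 wording give the time of contact, and nowhere is a 7-day recall period stated. This stands. A reader might infer that six or seven days of a defined seven-day outcome go unobserved, but no such window is defined. What can be said is that the row carries no restriction to the first hours, whereas the question does.
- **Role of the item.** The study does not aim to estimate a treatment effect, its objectives concern training, delivery, eligible numbers and recruitment materials, and the outcome sections do not define pain as an outcome. This stands and limits the weight of the point. In the text reviewed, Table 1 shows only its colour key, so no effect on a progression criterion can be shown.

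**Conclusion.** The point holds as a mismatch between two stated parts of the plan. Followed as printed, the 7-day contact would obtain early pain at best indirectly, would not obtain need for pain relief, and would miss pain arising or continuing after the first hours. Because the wording is common to everyone, this applies to all 40 planned participants. The number who would be misclassified cannot be estimated, since the article gives no expected frequency of pain after treatment.

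The conclusion assumes that the printed stem is the one used, and that no further systematic source exists outside the article. If the full questionnaire already asks about pain and pain relief since treatment, only the article's wording needs correcting.

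The importance is moderate. A reader might go further and treat first-week pain as the earliest sign of treatment failure, so that the study would miss its key safety signal. The documents do not say this, and related adverse events remain a partial route for later pain.

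**What to change.** Reword Question 2 so that it delivers the Table 2 row, in two short items:

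- (a) any pain from the treated tooth since treatment, and whether it is present now;
- (b) any pain relief taken for that tooth since treatment.

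Use the same wording for phone, text and email, and align the Table 2 key with the modes allowed in Participant reported outcomes. Because contact is from day 7 and may come later, record its date so that the length of recall is known.

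A pain score, and a question on unplanned dental contact for the tooth, are optional extras; the second goes beyond what the row lists.

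The cost is about one more minute per participant at a contact already planned, and a minor amendment to the questionnaire. If the sponsor wants only immediate post-operative problems, the alternative is to change the Table 2 row to say so. That costs less, but gives up pain relief and later pain as measured items.
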